### Randomisation

A computer-generated 1:1 block randomisation schedule has been produced by a statistician independent to the study, accommodating unequal recruitment across the four initial sites together with the possibility of additional trial sites. Secure, password-protected web-based randomisation will occur on patient arrival to a participating hospital trauma unit once inclusion and exclusion criteria have been assessed. Each patient will receive fibrinogen supplementation comprising either protocol-directed FC or Cryo therapy. Allocation concealment will be maintained through to the conclusion of the web randomisation process, but for practical and safety reasons, randomised trial patients and their treating health care professionals will not be blind to the trial intervention. Trial integrity will be supported by maintenance of blinding for outcome assessors and the trial statistician.

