### Intervention

After compliance with consent requirements and with the treating clinician’s approval, patients will be randomised to receive fibrinogen supplementation using either FC (Riastap®, CSL Behring GmbH, Marburg, Germany) or Cryo (Australian Red Cross Blood Service). The requirement for fibrinogen supplementation will be defined by a FIBTEM A5 (clot amplitude 5 min after clot formation) ≤10 mm together with a clinical scenario suggesting significant haemorrhage. The intervention will be performed in randomised patients as soon as possible after each FIBTEM threshold result becomes known. Patients will remain in their allocated intervention arm for the duration of their hospital admission up to 30 days. Dosing of FC and Cryo will be guided by the FIBTEM A5 result as per trial protocol (Fig. 1). FC will be administered by intravenous injection and Cryo by rapid intravenous infusion. Fibrinogen supplementation will be continued throughout the resuscitation according to protocol and as per the allocated intervention arm (Fig. 1).

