### Trial endpoints

The primary outcome is the time interval in minutes from FIBTEM analysis and clinical scenario suggesting that fibrinogen supplementation is required to the completion of the first administration of fibrinogen supplementation (FC or Cryo). It is aimed to administer the FC intervention within 30 min of fibrinogen requirement being identified. Consistent with the exploratory pilot nature of this study, multiple hypothesis-generating outcomes will be evaluated together with assessments of process feasibility, including:Effects of fibrinogen supplementation (FC and Cryo) on plasma fibrinogenTime to randomisationTime course of fibrinogen levels as measured by FIBTEM and Clauss Fibrinogen (FibC)Transfusion requirementsClinically relevant thromboembolic complicationsMortality at several time points including hospital discharge and 90 days

Detailed data collection will occur for the first 7 days of hospital admission and extended follow-up to 90 days (see the SPIRIT figure in Fig. 2). See Table 2 for full primary, secondary and feasibility outcomes.

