### Statistical analysis

Data analyses will be performed with a coded binary treatment indicator to preserve blinding to treatment allocation until the trial report is finalised by the writing committee. The trial primary and main secondary outcomes will be reported using intention-to-treat analyses based on all randomly assigned patients, except any who withdraw consent for use of all trial data.

Baseline variables will be summarised using descriptive statistics. The trial primary outcome and other time-to-event outcomes will be displayed as Kaplan-Meier curves and compared between treatments with Cox proportional hazards regression including, as covariates, the trial site stratification factor and patient age and sex. Sensitivity analyses will be performed using unadjusted Cox models which include a binary indicator of treatment as the only covariate, and also using multivariable Cox models including any other baseline covariates exhibiting substantial imbalance between randomisation arms. Lack of proportionality in any Cox model on testing will result in that outcome being assessed using a log-rank test and summarised using the Kaplan-Meier estimated median time to event [34]. Other secondary analyses, including assessment of the differential proportion of thromboembolic complications and mortality at specified time points, will be compared using either chi-square or Fisher exact tests, and also using logistic regression adjusting for the same covariates used in the Cox models. Results will be summarised using frequency tables, and risk ratios or odds ratios as appropriate, with 95% confidence intervals. Approximately normally distributed continuous variables (either untransformed or following log or other normalising transformation) will be compared using *t* tests, or otherwise compared using nonparametric methods (Mann-Whitney).

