A number of trials investigating FC use in non-traumatic haemorrhage have recently been published. The FIB-PPH trial reported no benefit to empiric FC (versus placebo) in patients with clinically significant postpartum haemorrhage; however, the mean plasma fibrinogen levels were >4 g/L [64]. The REPLACE trial investigating bleeding cardiac surgical patients also reported no benefit to FC [65]. The ZEPLAST trial, also in cardiac surgery, reported reduced bleeding and transfusion requirements in patients treated with a fixed dose of 6 g FC; however, subsequent analysis suggested that a smaller dose would likely have yielded the same results [66, 67]. These trials suggest that, based on clinical indications, it is difficult to predict those patients who will benefit from supplemental fibrinogen and there is no benefit in treating those who are not hypofibrinogenaemic. Therefore, it would seem logical to treat patients in whom hypofibrinogenaemia is contributing to ongoing haemorrhage and to dose-replace based on degree of hypofibrinogenaemia.

There is an expanding observational evidence base to support the use of FC in severe trauma, with recent academic literature reporting: increased clot strength, reduction in blood loss, reduced transfusion and mortality [14, 61, 68]. A recently published systematic review found limited evidence comparing FC to Cryo and concluded that it was not possible to recommend one product over another [69]. It is imperative that robust and clinically relevant trials are performed to investigate fibrinogen replacement strategies in severe trauma before widespread practice changes are implemented without a firm evidence base [70, 71].

The large doses of Cryo utilised in traumatic haemorrhage can put strain on local blood banks in supplying requested units in a timely manner. Additionally, the size of Australia introduces logistic challenges to the maintenance of adequate Cryo stocks to individual hospital blood banks. The use of a factor concentrate with a long shelf life and that is easy to use is an attractive option but at this time is not supported by good-quality evidence.

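### The primary Cox model leaves out pre-treatment FIBTEM A5, the value that guides the dose, and so plausibly gives up some power

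*Protocol article*

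**What the plan says.** All places are in the protocol article.

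- **Statistical analysis.** The primary outcome is compared by Cox regression "including, as covariates, the trial site stratification factor and patient age and sex". Sensitivity analyses use an unadjusted Cox model, "also using multivariable Cox models including any other baseline covariates exhibiting substantial imbalance between randomisation arms". If proportionality fails, the outcome goes to a log-rank test, with no covariates or strata mentioned.
- **Intervention.** "The requirement for fibrinogen supplementation will be defined by a FIBTEM A5 (clot amplitude 5 min after clot formation) ≤10 mm", together with a clinical picture of significant haemorrhage. "Dosing of FC and Cryo will be guided by the FIBTEM A5 result as per trial protocol"; the dose steps are in Fig. 1, which is not shown.
- **Trial endpoints.** The primary interval runs from the FIBTEM result and clinical need "to the completion of the first administration of fibrinogen supplementation (FC or Cryo").
- **Randomisation.** "web-based randomisation will occur on patient arrival to a participating hospital trauma unit once inclusion and exclusion criteria have been assessed". A FIBTEM result is not among the eligibility criteria in Table 1.
- **Discussion.** One gram of fibrinogen takes 3–4 units of whole-blood Cryo, and "The large doses of Cryo utilised in traumatic haemorrhage can put strain on local blood banks in supplying requested units in a timely manner".

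**The concern.** The outcome includes the time to prepare, issue and give the whole first dose, and A5 guides the size of that dose. A larger dose plausibly takes longer to complete, so the design itself points to A5 as a predictor of the interval. The covariate list instead has site, which is well justified as the stratification factor, and age and sex, which the article nowhere links to delivery time.

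The imbalance rule does not replace a prespecified covariate. It leaves the threshold for substantial imbalance undefined, is applied after the data are seen, reaches only a sensitivity model, and may not cover an A5 measured after randomisation, because it is limited to baseline covariates.

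What is at stake is power. The Sample size section fixes the total at 100 on recruitment and budget and warns that the observed SD will strongly influence power. Covariate choice is one of the few means of improving power that remain.

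**Working it through.** **1. The plan's own figures.** Inputs from Sample size: 50 per arm, SD 14 min, difference 8 min, alpha 5% (two-sided, according to the interim analysis section).

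- Standard error of the difference = 14 × √(2/50) = 2.8 min.
- Power = Φ(8/2.8 − 1.96) = Φ(0.897) = 81.5%, against about 80% stated.
- Detectable difference at 80% power = (1.960 + 0.842) × 2.8 = 7.84 min at SD 14, and 2.802 × 30 × √(2/50) = 16.8 min at SD 30. The plan states 8 and 17.

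The stated figures reproduce.

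**2. Gain in a comparison of means.** The documents give no A5–time correlation, so R², the share of within-arm variance in time explained by A5, is an assumption. With residual SD = 14 × √(1 − R²), R² of 0.10, 0.20 and 0.30 gives 13.28, 12.52 and 11.71 min, and power of 85.4%, 89.1% and 92.7%. The planned analysis is Cox, so these figures do not carry over directly.

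**3. Gain in the Cox model, linear A5.** Simulation: 50 per arm, normal times with SD 14, 8 min difference, no censoring, 2,000 trials per setting. Monte Carlo error on power is about 1 point: √(0.73 × 0.27/2000) = 0.010.

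| R² | Power without A5 | Power with linear A5 |
|---|---|---|
| 0 | 74.8% | 74.5% |
| 0.10 | 73.4% | 77.6% |
| 0.20 | 73.0% | 81.2% |
| 0.30 | 72.0% | 87.2% |

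The standard error of the log hazard ratio does not fall: about 0.208 without A5, and 0.211 to 0.213 with it at R² 0.10–0.30. Power rises because the conditional log hazard ratio is larger (0.53 to 0.58 at R² 0.10; 0.53 to 0.67 at R² 0.30). With no treatment effect, the rejection rate with linear A5 at R² 0.10–0.30 was 6.0–7.2%, against about 5% without, because normal times do not satisfy proportional hazards.

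**4. Gain with A5 strata.** The same set-up was repeated with 5,000 trials per setting and A5 cut at its tertiles to form strata. The tertiles stand in for the dose tiers, which are not shown. Power without A5 and with strata was 73.0% and 71.2% at R² 0; 74.0% and 75.5% at 0.10; 73.6% and 79.1% at 0.20; 73.2% and 82.4% at 0.30. The rejection rate under no effect was 5.0–5.7% with strata. Strata thus give a smaller gain than the linear term but hold the error rate better.

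**5. Chance imbalance.** The standardised A5 difference between arms has standard error √(2/50) = 0.2. The chance that it exceeds 0.2 SD is 2(1 − Φ(1)) = 32%, and that it exceeds 0.4 SD, 2(1 − Φ(2)) = about 5%. A 0.4 SD imbalance moves the mean difference by √R² × 14 × 0.4, which is 1.8 min at R² 0.10 and 3.1 min at R² 0.30, against a target of 8 min.

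**The case against.** **The model is valid, and covariates are often left to the SAP.** Validity stands: a stratification factor plus two fixed demographic covariates is prespecified and sound. On the SAP, the article does not leave the primary list open. It states the list, so the choice can be assessed.

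**The size of the gain is unknown.** This stands. Dose tiers, and time per vial or unit, are not shown. Triggered patients all have A5 of 10 mm or less, which limits its spread, and a very low A5 might prompt faster action that offsets a larger dose. The Discussion's remark on blood banks concerns the supply of large Cryo doses, not a gradient of time with A5. R² may be near 0.

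**A5 is not clearly a baseline variable.** This stands in part. Randomisation is on arrival, treatment follows each threshold result in patients already randomised, and a patient who never reaches the threshold has no triggering A5, although the analysis is by intention to treat. However, the primary clock starts at that A5, so a patient without one has no time origin either; the covariate does not create the gap. The first triggering A5 also precedes any study product, so the product cannot alter it.

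**Stronger readings that the documents do not support.** A reader might infer that leaving out A5 widens the confidence interval by a calculable amount. That is linear-model reasoning, and in the Cox model the standard error does not shrink when A5 is added. A reader might also infer that the primary estimate is biased by dose imbalance. Under randomisation, chance imbalance is imprecision, not bias, and the plan already has a sensitivity model for imbalanced baseline covariates. Nor is adjustment free: it needs a rule for patients who never trigger, and it changes the hazard ratio to one conditional on A5.

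**Conclusion.** The point holds as a minor to moderate efficiency matter. The plan omits from its primary model the one measured value that its own dosing rule and endpoint definition connect to the outcome, and could bring it in only by a data-driven route in a sensitivity model.

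The likely benefit is about 4 to 15 points of power with a linear term (77.6 − 73.4 and 87.2 − 72.0) and about 1.5 to 9 points with strata (75.5 − 74.0 and 82.4 − 73.2). This assumes that A5 explains 10–30% of the variance in time, that times are normal with SD 14, and that all 100 patients have a completed interval. If A5 predicts nothing, a linear term costs nothing and strata cost about 2 points.

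**What to change.** Before unblinding, prespecify pre-treatment FIBTEM A5 in the primary model alongside site, age and sex, preferably as strata defined by the protocol's dose tiers. Define the value in one of two ways:

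- **Admission A5**, so that every randomised patient should have a value. The Blood sampling section lists FIBTEM among the tests from admission onward. Add a rule for a missed sample.
- **First triggering A5**, which is known at the endpoint's time zero. State how patients who never reach the threshold are handled.

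Stratify the log-rank fallback by the same tiers, so that the gain survives if proportionality fails. Keep the unadjusted Cox model as the sensitivity analysis already planned; it also reports the hazard ratio that is not conditional on A5.

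The cost is small: A5 is already measured to guide dosing. The price is a hazard ratio conditional on A5; a type I error of about 6–7% if a linear term is used and proportional hazards fails, against about 5–6% with strata; and a small loss of power from strata if A5 is not prognostic.

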### Data and Safety Monitoring Committee and interim safety analysis

An independent Data and Safety Monitoring Committee (DSMC) will conduct two equally spaced interim analyses, at one third (*n* = 33) and two thirds (*n* = 67) of the time into trial recruitment, to assess the differential proportions of all-cause hospital mortality (censored at 30 days for practical reasons) observed in intervention (FC) compared with control (Cryo) patients.

These interim analyses will follow a group sequential plan (Fig. 4) employing symmetrical, two-sided, Haybittle-Peto, three-standard deviation thresholds to evaluate a standardised test statistic (|*Z*
_*k*_| ≥ 3) calculated from a normal approximation to the discrete binomial difference observed between treatment and control groups in mortality. Assuming no early stopping, *k* = 3 planned analyses will occur, with all-cause mortality assessed at *n* = 33, 67 and 100 patients (Fig. 4). Accounting for the type I error spent in these two interim mortality analyses, and in the absence of early stopping, a precise analysis of the trial primary outcome at full recruitment could be conducted at *p* < 0.048 (|*Z*
_*3*_| > 1.975) rather than the conventional statistical significance level (*p* < 0.05; |*Z*
_*1*_| > 1.96). However, in accord with common practice with a small number of interim analyses and symmetrical two-sided, three-standard deviation, Haybittle-Peto thresholds, this trial’s primary analysis will ignore the very small error spent conducting two interim analyses, and evaluate the final primary trial outcome at the conventional two-sided level of 0.05. The DSMC may conduct additional interim analyses of mortality or other outcomes at the committee’s discretion with adjustment to the final level of significance (*p* value) if required.

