There is growing evidence to support the use of VHA to rapidly guide targeted factor replacement in traumatic haemorrhage but data from RCTs is limited [41, 42]. A recent, single-centre RCT has reported significant reductions in blood product transfusion and improved survival with a VHA-guided MHP [43]. Whilst the evidence of a positive impact on mortality is equivocal, it is clear that VHA can be used to rapidly and reliably identify coagulopathic trauma patients [44, 45]. The FIBTEM assay can be utilised as a marker of TIC, predict massive transfusion and it correlates well with standard laboratory measures of fibrinogen concentration [11, 46, 47]. The present study will utilise the FIBTEM assay to identify patients with hypofibrinogenaemia and subsequently guide dosing of FC and Cryo. The FIBTEM A5 will be used to permit rapid intervention [48]. Each of the trauma centres involved in the trial have varying degrees of experience with VHA use in severe trauma [49]. This trial will utilise the ROTEM Sigma device (an automated cartridge-based system) to evaluate FIBTEM A5 and guide subsequent fibrinogen replacement. The location of the device either, at the point of care (POC) or in the laboratory environment, will depend on local logistical considerations and will be decided by each individual centre. Other blood product components will be administered as per each individual trauma centre’s standard MHP. Specifically, the use of tranexamic acid (TXA) as an intervention for hyperfibrinolysis will be as per standard practice at each individual trauma centre. The majority of Australian trauma centres are currently participating in the randomised controlled PATCH trial, investigating the prehospital use of TXA in severely injured trauma patients likely to have TIC [50]. Co-enrolment in PATCH and FEISTY has been agreed by both trial teams.

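### The non-proportionality rule is worded so broadly that a covariate or a sensitivity model could replace the site-adjusted primary analysis with a log-rank test that names no site stratification

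*Protocol article*

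**What the plan says.** All of the following is in the protocol article.

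- **Primary model** (Statistical analysis): Cox regression "including, as covariates, the trial site stratification factor and patient age and sex".
- **Further Cox models** (same section): "Sensitivity analyses will be performed using unadjusted Cox models which include a binary indicator of treatment as the only covariate", and a third type of model that adds baseline covariates found to be imbalanced.
- **Fallback** (same section): "Lack of proportionality in any Cox model on testing will result in that outcome being assessed using a log-rank test". The outcome is then "summarised using the Kaplan-Meier estimated median time to event". No strata are named and no adjusted estimate is kept.
- **Binary outcomes** (same section): these keep their adjustment, through "logistic regression adjusting for the same covariates used in the Cox models".
- **Sites** (Randomisation): the schedule was prepared "accommodating unequal recruitment across the four initial sites together with the possibility of additional trial sites".
- **Device location** (Discussion): "The location of the device either, at the point of care (POC) or in the laboratory environment, will depend on local logistical considerations".
- **Significance level** (section on the monitoring committee and interim analysis): the plan is to "evaluate the final primary trial outcome at the conventional two-sided level of 0.05".

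**The concern.** Two features of the rule deserve attention. Neither concerns how a log-rank test behaves when the treatment effect itself is non-proportional.

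**The trigger is wide.** Each time-to-event outcome may have three Cox models, and the primary one has six terms: treatment, three for site, age and sex. On a literal reading, non-proportionality of site, age or sex, or a failure seen only in a sensitivity model, is enough to displace the primary analysis, even when nothing is wrong with the treatment term.

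**The fallback drops site.** The document itself calls site a stratification factor. An unstratified log-rank test treats between-site variation in delivery time as noise, so the analysis no longer matches the randomisation. The total of 100 patients is fixed by recruitment and budget, so power lost this way cannot be bought back.

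**Working it through.** **1. The plan's own power figure.** Inputs from Sample size: 50 per arm, SD 14 min, difference 8 min, two-sided 5%.

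- Standard error = 14 × √(2/50) = 2.80 min. 8/2.80 − 1.96 = 0.897, giving power of 81.5% (80.8% with the noncentral t).
- Detectable difference at 80% power = (1.96 + 0.842) × 2.80 = 7.8 min. At SD 30 the standard error is 6.0 and the difference is 16.8 min.

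Both agree with the stated 80%, 8 min and 17 min. The sample size is not at fault.

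**2. How often the switch could happen.**

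- Six independent tests at 0.05 in the primary model: 1 − 0.95⁶ = 26% chance of at least one false trigger. One global test gives 5%.
- Simulated with exactly proportional hazards: 8–10% if a global test is run in all three models, 38–44% if every term of every model is tested, and 4–5% for the treatment term of the primary model alone.
- Simulated with normal times and the large site shifts of step 4: the global test in the adjusted model fires in 20–23% of trials, and the treatment term alone in 10–13%. Additive site shifts in normal times are themselves non-proportional, so the switch is likelier just where the fallback is weaker.

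**3. Power of the fallback if it were always used.** Assumptions: four sites of 40/28/20/12 patients, 1:1 within site, no censoring, 8 min effect, 3,000 trials per setting (Monte Carlo error about 0.8 points).

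| Between-site SD (min) | Plain v site-stratified log-rank, SD 14 within site | Plain v site-stratified log-rank, SD 14 in total |
|---|---|---|
| 0 | 75% v 74% | 74% v 73% |
| 5 | 69% v 74% | 75% v 79% |
| 7 | 65% v 73% | 76% v 85% |
| 10 | 57% v 72% | 79% v 95% |

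The protocol's SD is given per arm across sites, so the right-hand column is closer to the planned design. There the plain test does not fall below its value with no site difference. What is lost is the gain that stratifying would bring.

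**4. Power of the whole rule.** The fallback runs only when the trigger fires, so the relevant comparison is the full procedure: adjusted Cox unless a global test in the primary model fails, then plain log-rank. It is set against the narrower trigger with a stratified fallback. Sites are 40/30/20/10, with 1,500 trials per setting.

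| Assumed site shifts (min) | Plan v fix, SD 14 within site | Plan v fix, SD 14 in total |
|---|---|---|
| 0/10/−10/0 | 74% v 77% | 82% v 85% |
| 0/15/−10/5 | 70% v 75% | 89% v 93% |
| 0/20/20/0 | 68% v 73% | 91% v 95% |

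In the middle column the site shifts are added to an SD of 14, so total SDs become √(196+49) = 15.7, √(196+81) = 16.6 and √(196+100) = 17.2 min.

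The gaps in the table are 3 to 5 points. Allowing for simulation error and a repeat run, the loss is about 3–6 points, and up to 7–8 if the unadjusted model can also trigger the switch. With shifts of about 5 min it is 1–2 points; with none, 0–1 point.

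**5. Type I error.** With no treatment effect and a between-site SD of 10 min, the plain log-rank test rejects in about 2% of trials, the site-stratified log-rank in about 6% and the adjusted Cox Wald test in 8.4%. The plain test is conservative. Because the Cox test is somewhat liberal at this size, the stratified log-rank is the fairer comparator in step 3.

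**The case against.** The strongest reply is that much of this depends on reading the sentence unfavourably.

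- **Strata.** The document does not call the log-rank test unstratified, and an analysis plan that is not shown may stratify it. This stands as a caution. But the text does state a rule that replaces the adjusted model, and the same section says explicitly that adjustment is kept for the logistic models.
- **Trigger.** The word any may simply range over the several time-to-event outcomes, and nothing says that each term is tested separately. This also stands. A reader might infer that the switch would occur by chance in some 40% of trials, but that figure needs term-by-term testing in all three models, which the document does not prescribe.
- **Site differences.** A reader might infer from the choice of device location that delivery times must differ by site. The support is weak. Under Trial endpoints the primary interval starts from the FIBTEM analysis together with the clinical picture, so transport of the sample to a laboratory falls largely before the clock starts. Delay in passing on the result could still count, but no document figure supports shifts of 10 to 20 min.
- **Size.** A reader might take the gaps in step 3, 15 points or more, as the cost. They assume that the fallback always runs, and the largest losses against the planned power also come from adding site variance to an arm-level SD. Neither follows from the document.
- **Setting.** This is an exploratory pilot sized by recruitment and budget.

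**Conclusion.** The point holds as a defect of wording with a modest cost. As written, the rule allows a covariate or a sensitivity model to replace the site-adjusted primary analysis with one that ignores the stratifier.

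The expected cost of the whole rule is about 3–6 power points if site means differ by 10–20 min, up to about 8 if a failed sensitivity model also counts, 1–2 points at about 5 min, and essentially nothing if sites do not differ. These figures rest on assumed site shifts, normal delivery times, no censoring and an 8 min effect.

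It would be wrong to infer that the rule inflates false positives, since the plain test is conservative when sites differ. It would also be wrong to infer that power falls below plan wherever sites differ: with a total SD of 14 min it does not. Priority: consider.

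**What to change.** Replace the fallback sentence, in the protocol or the analysis plan, with a rule to this effect:

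1. The proportionality test that governs the analysis is that of the treatment term in the primary adjusted model only.
2. A non-proportional covariate is handled by stratifying the Cox model on it. Age would need bands fixed in advance.
3. If the treatment term fails, the test is a log-rank test stratified by trial site.

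The change needs a few lines of text and no extra data. If sites do not differ at all, stratifying costs about 0–3 power points: 76% stays 76% under normal times, and 82% becomes 79% under proportional hazards.
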